### Study endpoints

The primary endpoint of the study will be to evaluate whether HFNT is noninferior to NIV in reducing PaCO_2_, at 2 h after the group allocation, in patients with exacerbation of COPD and mild-to-moderate respiratory acidosis. The secondary endpoints will be: noninferiority of HFNT to NIV in reducing PaCO_2_ at 6 h after randomization; dyspnea score; treatment failure rate; discomfort related to the interface or to symptoms related to airway and mouth dryness; respiratory rate; need for endotracheal intubation; time spent under mechanical ventilation (both invasive and NIV); ICU and hospital length of stay; and hospital mortality.

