### Intervention group

Patients randomized to the intervention group will receive HFNT (Optiflow and MR850 or AIrVO_2_™; Fisher & Paykel Healthcare, Auckland, New Zealand), initially set at 60 L/min and a temperature of 37 °C. In the case of discomfort, the flow and/or temperature will be downregulated to the most tolerated setting. In the HFNT group, a rescue NIV treatment will be allowed in the case of worsening of respiratory failure and/or treatment failure, before proceeding with an eventual endotracheal intubation and invasive mechanical ventilation.

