### Control group

Patients randomized to the control group will receive NIV applied through a total full-face or oro-nasal mask. The ventilator will be set in pressure support ventilation (PSV) mode, with positive end-expiratory pressure (PEEP) between 3 and 5 cmH_2_O. The inspiratory pressure support will be regulated in order to achieve a measured or estimated tidal volume equal to 6–8 ml/kg of ideal body weight [35]. The treating physicians, based on local availability, will choose the ventilators used to deliver NIV.

In both groups, treatment other than ventilatory support will be supplied according to current guidelines [1]. Sedatives will be allowed to improve the patient’s comfort and tolerance of the interfaces. The inspired oxygen fraction (FiO_2_) will be set to maintain a peripheral saturation (SpO_2_) target between 88 and 92% [1]. In the case of treatment interruption due to any reason, patients will receive oxygen supply through a Venturi mask to achieve the same SpO_2_ target. During study interventions, patients will be monitored by at least continuous SpO_2_, electrocardiogram and noninvasive blood pressure.

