### Data collection and outcome assessment

For each patient, we will collect anthropometric data (age, gender, weight and height) and baseline characteristics (the Simplified Acute Physiology Score (SAPS II), the Kelly-Matthay score [36], the Charlson index [37] and the Richmond Agitation Sedation Scale (RASS) score [38]). Furthermore, soon before randomization we will record vital parameters (heart rate, blood pressure, breath frequency and temperature), the amount of secretions, the presence of dyspnea (as reported by the patient through the Borg scale) [39] and arterial blood gases (ABGs) at patient inclusion.

At 2 and 6 h after the patient’s randomization to receive NIV or HFNT, we will collect all vital parameters, ABGs, the RASS score, the Kelly-Matthay score [36], the grade of dyspnea and the need for sedatives. Sedation will be allowed to increase tolerance to the treatment [40, 41]. Moreover, we will record: the settings of NIV and HFNT; the discomfort related to the interface, as assessed through a 11-point Numeric Rating Scale (NRS) [15, 42, 43]; and the intolerance to the interface due to flow, temperature, noise, claustrophobia, sweating, tightness, airway dryness, vomiting gastric distension, ocular irritation or skin breakdown, separately [42, 44, 45].

We will also record: the rate of treatment intolerance, as defined by the inability of the patient in continuing NIV or HFNT treatment; the rate of treatment failure, as defined by the presence of PaCO_2_ worsening or reduction < 10 mmHg from baseline assessment, or worsening or no improvement of dyspnea, or respiratory rate > 30 breaths/min; need for endotracheal intubation; time spent under mechanical ventilation (both invasive and NIV); ICU and hospital length of stay; and hospital mortality.

The decision to intubate the patient will be taken by the physician in charge of the patient, in the case of the presence of one of the following criteria: respiratory arrest, respiratory apnea or pauses with loss of consciousness, severe agitation, bradycardia (< 50 beats/min) with loss of consciousness, hemodynamic instability with systolic arterial pressure < 70 mmHg, need for invasive mechanical ventilation due to worsening in arterial blood gases and pH, need for suctioning due to unmanageable secretions or intolerance to all of the interfaces (including shift of treatment to NIV in the HFNT group).

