### Statistical analysis

For the purpose of the study, we computed a sample size of 56 patients, given an α error of 5% (one-sided) and a β error of 80%, with a standard deviation for the primary outcome equal to 15 mmHg and a noninferiority limit of 10 mmHg [35]. After considering potential drop-outs (30%) [35] and an increase in sample size for nonparametric analysis (15%), the final computed sample size was 80 patients (40 per group).

An independent investigator, blinded to treatment allocation, will undertake all statistical analyses on an intention-to-treat basis. After checking the Gaussian distribution, continuous data will be presented as mean (standard deviation) or median (25th–75th IQR).

Categorical data will be expressed as count and percentage. Continuous data will be compared by the Mann–Whitney *U* test or the Student *t* test, and categorical data by the chi-square test or the Fisher exact test [46]. The Kruskal–Wallis test will be used to check between-group differences at baseline, 2 h and 6 h. Friedman’s test or repeated-measures ANOVA will be used to check within-group differences at different time points. *p* < 0.05 will be considered significant.

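### The secondary endpoint of time under mechanical ventilation counts the control arm's allocated NIV but no HFNT time, so with equal support need it tends to favour HFNT by construction

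*Protocol article*

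**What the plan says.** The Study endpoints section of the protocol article names, among the secondary endpoints, "time spent under mechanical ventilation (both invasive and NIV". The Data collection and outcome assessment section repeats the definition in the list of recorded outcomes: "need for endotracheal intubation; time spent under mechanical ventilation (both invasive and NIV); ICU and hospital length of stay; and hospital mortality". Neither place has a rule that differs by arm.

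The allocated treatments are:
- Control group section: "Patients randomized to the control group will receive NIV applied through a total full-face or oro-nasal mask".
- Intervention group section: "Patients randomized to the intervention group will receive HFNT". The same section adds that "a rescue NIV treatment will be allowed in the case of worsening of respiratory failure and/or treatment failure", ahead of any intubation.

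The Statistical analysis section states that "Continuous data will be compared by the Mann–Whitney *U* test or the Student *t* test", and that an independent blinded investigator "will undertake all statistical analyses on an intention-to-treat basis". It makes no exception for this endpoint.

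**The concern.** The parenthesis in the endpoint settles what is counted: invasive ventilation and NIV. NIV is the control treatment and HFNT is not on the list. One arm's counter starts with its allocated treatment, while the other arm's starts only when its allocated treatment is abandoned or supplemented. Two patients with the same clinical course, both supported for the same number of hours and neither failing, would score their full support time in one arm and zero in the other.

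This is a stated rule and not a missing detail. An analysis plan that applied the definition faithfully would carry the asymmetry through.

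At stake is how one secondary result is read. The endpoint stands beside intubation, length of stay and hospital mortality, and the Discussion concedes that the physiological primary outcome leaves the clinical outcomes uncertain. A shorter ventilation time under HFNT could then be taken as a sign of faster recovery when part or all of it follows from which device was allocated.

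**Working it through.** **The plan's own figure.** The article gives no figure for ventilation time. Its only calculation is the base sample size for PaCO2, which reproduces: per arm 2 × [15 × (1.645 + 0.842) / 10]² = 27.8, rounded up to 28, so 56 in total. That figure does not depend on the endpoint discussed here.

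**Step 1: what counts in each arm.** Let T be the hours of respiratory support a patient needs, with the same distribution in both arms.
- Control: counted time = T, since the allocated support is NIV (Control group section).
- HFNT, neither rescued nor intubated: counted time = 0.
- HFNT, rescued at time s: counted time = T − s, or 0 if T is shorter than s (Intervention group section).

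No section removes the allocated NIV, adds HFNT hours, or limits the endpoint to ventilation after failure.

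**Step 2: what follows without further inputs.** If the proportion r rescued or intubated is below one half, more than half of HFNT patients score 0, so the HFNT median is 0 h. For the HFNT mean to equal the control mean, rescued patients must average 1/r times the control duration: 5 times at r = 20%, 3.3 times at 30%, 2 times at 50%.

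**Step 3: illustrative size.** The documents give neither r nor T, so these are assumptions: T log-normal with median 24 h and log-SD 0.8, rescue at s = 2 h, r varied, 40 per arm as planned. The mean of T is 24 × exp(0.8²/2) = 24 × 1.377 = 33.0 h. The ratio of counted means is then about r × (33.0 − 2)/33.0 = 0.94 × r.

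A simulation of 2,000 trials per rescue rate, with no true difference in support need and a two-sided Mann–Whitney test at 0.05, gave:

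| Rescue rate r | 0.94 × r | Simulated mean ratio, HFNT/control | Trials significant in favour of HFNT |
|---|---|---|---|
| 20% | 0.19 | 0.19 | 100% |
| 30% | 0.28 | 0.29 | 100% |
| 50% | 0.47 | 0.48 | 99% |
| 70% | 0.66 | 0.67 | 77% |
| 100% | 0.94 | 0.95 | 7.6% |

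The simulated ratios lie slightly above the formula because the average of ratios exceeds the ratio of averages. At 100% rescue the remaining gap is the first 2 h on HFNT, which are not counted. The percentages belong to these inputs. Only the direction under equal support need follows from the definition itself.

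**The case against.** The strongest reply has four parts.

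*The endpoint is honestly labelled.* It is time on a ventilator, not time on respiratory support. Hours on NIV are a real burden, and the Discussion gives poor comfort and poor patient–ventilator interaction as reasons for the trial. This stands as a reason to report NIV hours. It does not justify a between-group test in which one arm's allocated treatment is the thing counted.

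*The measure does respond to HFNT failure.* Rescue NIV and invasive hours count in both arms. A reader might infer that the endpoint merely restates the allocation and carries no outcome information. That goes too far: many or long rescues would lengthen the HFNT total and could cancel or reverse the tilt.

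*Nobody knows the rescue rate.* A reader might infer that the trial is bound to report a large and highly significant reduction. The documents do not support this. Rescue is permitted for worsening or treatment failure, and failure is defined broadly: a PaCO2 fall of less than 10 mmHg, dyspnoea that does not improve, or a respiratory rate above 30 each suffices. Rescue could be common, and in the illustration the effect shrinks as it becomes so. The objection stands against certainty about size, not against the direction under equal support need.

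*It is one of several secondary endpoints.* The primary comparison is PaCO2 at 2 h, and the Discussion leaves major clinical outcomes to later trials. This also stands and limits the weight of the point.

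A reader might further infer that early deaths will be scored as short, favourable durations for ventilation time and length of stay. The Statistical analysis section has only a general sentence on continuous data and says nothing about deaths. An article commonly leaves that to the full protocol or analysis plan, so no fault can be drawn from it here.

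**Conclusion.** The concern holds in a limited form. The definition, given in two sections without an arm-specific rule, counts the control arm's allocated treatment and omits HFNT time. If both arms need the same duration of support, the between-group test tends to favour HFNT for that reason alone.

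The size is conditional. An HFNT median of 0 h requires only that fewer than half of HFNT patients are rescued or intubated. The mean ratio of about 0.2 to 0.7 at rescue rates of 20% to 70% rests on the assumed support distribution and the assumed 2 h rescue time, and frequent or prolonged rescue could offset it. The primary endpoint, the sample size and the noninferiority conclusion are untouched.

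**What to change.** 1. Make the between-group comparison on invasive ventilation time, which is defined alike in both arms.
2. Where HFNT start and stop times are available, also compare total time on any support (HFNT + NIV + invasive) from randomisation. State one rule for interruptions that applies to both arms, since the Control group section foresees periods on Venturi oxygen when treatment is interrupted.
3. Report NIV time by component (allocated NIV in controls, rescue NIV in the HFNT arm) descriptively, with the asymmetry stated, and do not test the combined NIV-plus-invasive measure between arms.

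Items 1 and 3 cost a change of endpoint wording, provided that invasive and NIV hours are recorded separately. Item 2 needs HFNT start and stop times. The Data collection and outcome assessment section mentions device settings at 2 and 6 h but not stop times, and the Trial status section shows that recruitment began in March 2018, so these times may be incomplete for patients already enrolled. Because the trial is unblinded and under way, the change should be dated and documented as made before any comparison of the arms.

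### Deaths enter the ICU and hospital stay comparisons as stays that end at death, so an arm with more early deaths can appear to have the shorter stay

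*Protocol article*

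**What the plan says.** In the protocol article, Study endpoints closes the list of secondary endpoints with "ICU and hospital length of stay; and hospital mortality". Data collection and outcome assessment says that the same items will be recorded.

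Statistical analysis does not name length of stay. It gives one between-group rule for all measurements of this kind: "Continuous data will be compared by the Mann–Whitney *U* test or the Student *t* test". Mortality falls under the separate rule for counts: "categorical data by the chi-square test or the Fisher exact test". The blinded analyst "will undertake all statistical analyses on an intention-to-treat basis", and summaries are a mean with SD or a median with quartiles, with no restriction to survivors.

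No section gives deaths a value or rank in the stay endpoints, treats death as a competing event, or requires stay and mortality to be read together.

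**The concern.** A short stay is good news when it ends in discharge home and bad news when it ends in death. A test on the raw number of days cannot tell the two apart. Dropping the deaths does not solve this, because survivors in the two arms are no longer groups formed by randomisation.

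The direction matters in this trial. The Background credits NIV with lower mortality and a shorter ICU stay, and the trial asks whether HFNT can stand in for NIV. If HFNT led to more early deaths, the stated comparison would shift stay in HFNT's favour, on an outcome where the article itself cites a benefit of NIV. The Discussion expects the results to feed the design of later trials on major clinical outcomes, so a misleading stay estimate could be carried forward.

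**Working it through.** **The plan's own figure.** No calculation is given for stay or mortality. The only sample size is for PaCO2, with "standard deviation for the primary outcome equal to 15 mmHg and a noninferiority limit of 10 mmHg", one-sided α 5%, and the stated 80% read as power: 2 × (1.645 + 0.842)² × 15² / 10² = 27.8, so 28 per arm and 56 in total, as stated. The final 80 equals 56 / 0.7. Only the 40 per arm is used below.

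**Assumptions (none from the documents).** Stay in patients who live is log-normal with median 10 days and log-SD 0.6, the same in both arms. Time to death is 0.3 days plus an exponential with mean 3, 6, 10 or 14 days. Mortality is 5% versus 15%.

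**Mean stay in closed form.** Mean stay in survivors is 10 × exp(0.6² / 2) = 11.97 days. With deaths at about day 3 (mean 3.3):
- 5% mortality: 0.95 × 11.97 + 0.05 × 3.3 = 11.5 days
- 15% mortality: 0.85 × 11.97 + 0.15 × 3.3 = 10.7 days

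In general the shift in the higher-mortality arm is (0.15 − 0.05) × (mean time to death − 11.97). It is negative only while deaths come, on average, before the mean discharge of survivors. It is zero when the two coincide, and then changes sign.

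**Simulation, 40 per arm.** The table shows how often the higher-mortality arm looks better on raw stay. Significant means a two-sided 5% Mann–Whitney test in that direction.

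| Mean time to death | Shift in mean stay (formula) | Shorter median | Significantly shorter |
|---|---|---|---|
| about 3 days | 0.10 × (3.3 − 11.97) = −0.87 | 67% | 10% |
| about 6 days | 0.10 × (6.3 − 11.97) = −0.57 | 62% | 6% |
| about 10 days | 0.10 × (10.3 − 11.97) = −0.17 | 56% | 5% |
| about 14 days | 0.10 × (14.3 − 11.97) = +0.23 | 50% | 2% |
| no effect | 0 | 50% | 2.5% |

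A repeat with 6,000 trials per row gave 68%, 61%, 54% and 51% for the median, and 9%, 6%, 3% and 3% for significance. The simulated columns are therefore good to about two percentage points.

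**Deaths ranked worst.** With mortality 5% versus 15%, the higher-mortality arm then has the shorter median in about 30% of trials and is significantly shorter in about 0.3%. The figure lies below 50% because this comparison counts the extra deaths against that arm, as intended.

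**Other mortality gaps, deaths at about day 3.**
- 10% versus 25%: shorter median in about 77% of trials on raw stay, 20% with worst rank; significantly shorter in 15% on raw stay.
- 5% versus 10%: 59% and 40%; significantly shorter in 4.6%.
- 10% versus 10%: 50% and 50%, so no distortion.

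**Second model.** With median stay 9 days, exponential time to death with mean 2 or 4 days, and mortality 10% versus 20%, the figures are 69–71% on raw stay and 29% with worst rank.

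**The case against.** **This is detail for an analysis plan.** The article is condensed, its continuous-data sentence is generic, and intention to treat fixes the arm in which a patient is analysed, not the value given to a death. A reader might infer that the protocol states that a death on day 2 scores as a two-day stay. It does not; that follows only from applying its general rule to stay, and an unseen analysis plan could add a rule for deaths. What remains is that the article does choose a test and a population, no other method in it fits stay, and following them has the effect described. The point is about that stated method, not about missing detail.

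**The effect is not automatic.** A reader might infer that the result is biased whenever mortality differs. The working shows otherwise: with mean time to death near 14 days the distortion is gone, and mean stay is slightly longer in the arm with more deaths. The documents give no timing of death, so nothing in them supports the unconditional statement. This objection stands, and the point is limited accordingly.

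**The percentages look larger than they are.** The shorter-median figures must be read against 50%. A false significant result is much less common: 10% at most in the 5% versus 15% table, against 2.5% by chance. This also stands.

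**Little depends on these endpoints.** They are secondary, the primary is PaCO2 at 2 h, and the Discussion concedes that a physiological outcome leaves patient-related outcomes uncertain. Hospital mortality is listed beside stay, so excess deaths would be visible. That helps a careful reader but does not correct the test or the median. A reader should not infer that the noninferiority conclusion is at risk, or that the documents suggest HFNT raises mortality; they support neither.

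**Conclusion.** The point holds in conditional form. If mortality differs between arms and deaths come earlier than typical discharge, the stated comparison shifts ICU and hospital stay in favour of the arm with more deaths. Under the assumptions above and mortality 5% versus 15%, that arm shows the shorter median in about 67% of trials with deaths at about day 3, falling to 50% at about day 14. A significantly shorter stay falls from about 10% to the chance level.

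The actual size is unknown, because the documents give no mortality, stay or timing of death. The simulated stay was not modelled separately for ICU and hospital. For ICU stay the same condition applies relative to typical ICU discharge. This is a cheap improvement on secondary endpoints, not a threat to the primary result.

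**What to change.** State in Statistical analysis how deaths enter both stay endpoints, before the data are analysed. Either of these would do:

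- Compare ICU and hospital stay by Mann–Whitney with in-hospital death ranked worse than any observed stay.
- Analyse time to discharge alive, from ICU and from hospital, with death as a competing event.

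Report raw stay in survivors as description only, next to mortality in each arm.

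Worst rank needs only stay and hospital mortality, which Data collection and outcome assessment already lists. For the ICU version of the second option, check that the case report form shows whether a death occurred in the ICU. Days alive and out of hospital to a fixed day is open only if status after discharge is collected, and the article mentions in-hospital outcomes only.

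The cost is a change of wording. The downside is a less familiar summary than median stay, and one that partly overlaps with the mortality endpoint.

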### Data collection and outcome assessment

For each patient, we will collect anthropometric data (age, gender, weight and height) and baseline characteristics (the Simplified Acute Physiology Score (SAPS II), the Kelly-Matthay score [36], the Charlson index [37] and the Richmond Agitation Sedation Scale (RASS) score [38]). Furthermore, soon before randomization we will record vital parameters (heart rate, blood pressure, breath frequency and temperature), the amount of secretions, the presence of dyspnea (as reported by the patient through the Borg scale) [39] and arterial blood gases (ABGs) at patient inclusion.

At 2 and 6 h after the patient’s randomization to receive NIV or HFNT, we will collect all vital parameters, ABGs, the RASS score, the Kelly-Matthay score [36], the grade of dyspnea and the need for sedatives. Sedation will be allowed to increase tolerance to the treatment [40, 41]. Moreover, we will record: the settings of NIV and HFNT; the discomfort related to the interface, as assessed through a 11-point Numeric Rating Scale (NRS) [15, 42, 43]; and the intolerance to the interface due to flow, temperature, noise, claustrophobia, sweating, tightness, airway dryness, vomiting gastric distension, ocular irritation or skin breakdown, separately [42, 44, 45].

We will also record: the rate of treatment intolerance, as defined by the inability of the patient in continuing NIV or HFNT treatment; the rate of treatment failure, as defined by the presence of PaCO_2_ worsening or reduction < 10 mmHg from baseline assessment, or worsening or no improvement of dyspnea, or respiratory rate > 30 breaths/min; need for endotracheal intubation; time spent under mechanical ventilation (both invasive and NIV); ICU and hospital length of stay; and hospital mortality.

The decision to intubate the patient will be taken by the physician in charge of the patient, in the case of the presence of one of the following criteria: respiratory arrest, respiratory apnea or pauses with loss of consciousness, severe agitation, bradycardia (< 50 beats/min) with loss of consciousness, hemodynamic instability with systolic arterial pressure < 70 mmHg, need for invasive mechanical ventilation due to worsening in arterial blood gases and pH, need for suctioning due to unmanageable secretions or intolerance to all of the interfaces (including shift of treatment to NIV in the HFNT group).

Data will be collected on a dedicated case report form that will be sent to the data manager in de-identified form. The data manager will be responsible for entering data into a dedicated database, to code and store them. Treatment allocation will also be processed in order for the independent investigator in charge of the statistical analysis to be blinded.

